## Abstract

**Introduction:**

‘Let’s Talk About Children’ is a brief family focused intervention developed to improve mental health outcomes of children of parents with mental illness (COPMI). This study aims to assess the efficacy of LTC in improving mental health of children of parents with schizophrenia or bipolar disorder in China.

**Methods:**

The planned study is a multicentre parallel group randomized wait-list controlled trial. A total of 400 eligible families with children aged 8 to 18 years will be recruited, 200 each for families with parental schizophrenia or bipolar disorder. The intervention group will receive Let’s Talk About Children delivered by a trained therapist, while the control group will receive treatment as usual. The primary outcomes are child mental health measured by the strengths and difficulties questionnaire and parent–child communication measured using the parent-adolescent communication scale. Parental mental health and family functioning are secondary outcomes. This study also plans to explore mediating factors for the effect of Let’s Talk About Children on child mental health, as well as conduct a cost-effectiveness analysis on using Let’s Talk About Children in China.

**Conclusion:**

The present study will provide evidence for the efficacy of Let’s Talk About Children in families with parental schizophrenia and bipolar disorder in China. In addition, it will evaluate potential mechanisms of action and cost-effectiveness of Let’s Talk About Children, providing a basis for future implementation.

**Trial registration:**

ChiCTR2300073904.

## Introduction

Up to one in five children and adolescents worldwide are growing up in families where at least one parent experiences mental illness [1]. Children of parents with mental illness (COPMI) not only have a higher genetic risk for the condition, but on average also experience more childhood adverse events including emotional abuse, domestic violence and bullying [27]. Studies also show that mental illnesses amplify parenting challenges, may interfere with parent–child bonding, and can lead to children to taking on household burdens incongruous with their developmental age [6, 7, 13, 14, 18]. These factors impair the family’s ability to nurture child growth and may contribute to the transgenerational transmission of mental health conditions. Children whose parents experience severe mental disorders such as schizophrenia or bipolar disorder are especially disadvantaged and are at greater risk of having poorer outcomes in adulthood than children of parents without a mental health condition. Across multiple studies, the proportion of children with familial high risk who develop schizophrenia in adulthood ranges from 12.3% to up to 18.8% [11, 13, 21], compared to less than 1% in the general population [16].

Research has been conducted to identify modifiable risk factors that may potentially prevent or attenuate symptoms of mental disorders in offspring of parents with mental illness. Poor parenting behaviour and family functioning have been found to mediate the associations between parental mental disorder and offspring mental health outcomes [3]. Lack of appropriate information and support may lead to COPMI feeling guilty for causing their parent’s illness, which can in turn negatively affects their own emotions and behaviours [26]. These findings suggest that improving parenting capabilities and increased communication about parental mental health conditions may potentially improve outcomes for COPMI. However, many parents with mental illnesses lack parenting support tailored to their needs and also do not have the confidence to talk about their conditions with their children [19, 20].

In response to this issue, several family focused practices have been developed to support parents with mental health conditions and subsequently improve the mental well-being of COPMI [28]. One of these interventions is Let’s Talk About Children (LTC). LTC is a brief program designed to be delivered in low resource settings to help parents with mental illnesses build protective relationships with their children and improve family functioning [1, 2]. Evidence shows that LTC decreases depression and anxiety and increases prosocial behaviour and health related quality of life in COPMI [10, 24]. LTC also improves parental motivation to engage with mental health treatment, and increases their self-acceptance and parenting confidence [26]. These positive effects may potentially prevent future mental illness in COPMI as well as increase resilience if mental health issues may occur.

Previous applications of LTC have been largely in families where parent(s) suffer from depression [10, 24]. We found only one study on the efficacy of LTC in families with parental bipolar disorder [28] and none in families with parental schizophrenia, despite the greater disadvantage faced by children in these circumstances. Moreover, LTC has been implemented in various countries including Finland [24], Greece [10], Japan [26], Australia [19] and the USA [20], however, it has not yet been translated into Chinese. Mental health services in China generally focus on the treatment of patients with clinically diagnosed conditions. There is a lack of evidence-based therapies that can be used in children at high risk or exhibiting subthreshold symptoms of mental disorders in China. Our team has previously translated and adapted LTC for use in China. A pilot feasibility study of 30 COPMI families found that LTC increased parenting confidence and improved parenting satisfaction in 60% and 90% of participating families respectively (unpublished data). This study aims to bridge this knowledge gap by conducting a randomized controlled trial (RCT) to investigate the effects of LTC in families with parental schizophrenia or bipolar disorder in China.

## Objectives

The primary objective of this study is to assess the efficacy of LTC in improving mental health of children of parents with schizophrenia or bipolar disorder in China. We hypothesize that the 3-session LTC intervention will result in improvements in child mental health or parent–child communication compared to a wait list control group.

The secondary objectives are to:Assess the efficacy of LTC in improving the mental health of parents experiencing schizophrenia or bipolar disorder.Explore potential mechanisms of action for improvement of child mental health using LTC. A proposed causal pathway is presented in Fig. 1.Assess the cost effectiveness of LTC in families with parental schizophrenia or bipolar disorder in China.

**Fig. 1 Fig1:**
[figure not shown]
Hypothesized mechanisms of action for improvement of child mental health using ‘Let’s Talk about Children’

## Methods

### Design

A flowchart of the study design is shown in Fig. 2. The WHO Trial Registration Data Set is provided in Table 1. The planned study is a multicentre parallel group randomized wait-list controlled trial. A total of 400 eligible families with children aged 8 (inclusive) to 18 (not inclusive) years will be identified and recruited, 200 each for families with parental schizophrenia or bipolar disorder. The study was approved by the Ethics Committee of Peking University Institute of Mental Health, reference number 2023(51). This trial is registered in the Chinese Clinical Trial Registry (ChiCTR), ChiCTR2300073904. This study was initiated by [name] and is funded through a research grant from the China Medical Board (grant #21–435). The coordinating centre (Peking University Institute of Mental Health) will conduct intervention training, random sequence generation, data management, quality control, audit trial conduct and supervise intervention implementation. This protocol is reported in accordance with Spirit guidelines [5].

**Fig. 2 Fig2:**
[figure not shown]
Study design

**Table 1 Tab1:** Summary of study design

Data category	Information
Primary registry and trial identifying number	ChiCTR ChiCTR2300073904
Date of registration in primary registry	2023–07-25
Secondary identifying numbers	Protocol number CAFF20230725
Source(s) of monetary or material support	China Medical Board
Primary sponsor	China Medical Board
Secondary sponsor(s)	Care for Families Program (Beijing, China)
Contact for public queries	[name], MPH, [contact]
Contact for scientific queries	[name], MPH, [contact]
Public title	"Let’s Talk About Children" Family Focused Intervention for Children of Parents with Severe Mental Disorders: Protocol for a Randomized Controlled Trial
Scientific title	"Let’s Talk About Children" Family Focused Intervention for Children of Parents with Severe Mental Disorders: Protocol for a Randomized Controlled Trial
Countries of recruitment	China
Health condition(s) or problem(s) studied	Schizophrenia, Bipolar Disorder
Intervention(s)	Intervention group: Let’s Talk about Children; Control group: Treatment as usual, which typically includes medication, case management, outpatient consultations and rehabilitation services;
Key inclusion and exclusion criteria	Inclusion criteria are: 1. At least one child that is at least 8 years old and not yet 18 years old in the family; 2. One biological parent has met ICD-10 diagnostic criteria for schizophrenia or bipolar disorder for at least one year; 3. In the past year, the patient has lived with the child(ren) for at least 6 months; 4. Patient and their child(ren) can understand the study and provide written informed consent Exclusion criteria are: 1. Previous or current participation in family therapy; 2. Patient has been hospitalized or has visited the emergency room in the past month due to their mental illness, or presence of self-harm, suicidal or aggressive behaviour in the past month; 3. Patient or their child(ren) has severe cognitive impairment, learning disabilities, communication difficulties or behavioural problems; 4. Anticipated difficulty in completing the intervention or follow-ups for the next 7 months for any reason (i.e., moving away); 5. Single parent households at the time of enrolment (parent is divorced or widow(er)ed and is not remarried); 6. Both parents suffer from severe mental illnesses, including schizophrenia, bipolar disorder, schizoaffective disorder, delusional disorder, or other psychotic disorders Discontinuation criteria: 1. During the intervention or follow-up period, patient is hospitalized or visits the emergency room due to their mental illness, or exhibits self-harm, suicidal or aggressive behaviour, or is diagnosed with other severe medical conditions; 2. During the intervention or follow-up period, the spouse or child(ren) is diagnosed with a severe mental disorder (including schizophrenia, bipolar disorder, schizoaffective disorder, delusional disorder, or other psychotic disorders), or other severe medical conditions
Study type	Randomized Clinical Trial
Date of first enrolment	September, 2023
Target sample size	400
Recruitment status	Ongoing
Primary outcome(s)	Strengths and Difficulties Questionnaire; Parent-Adolescent Communication Scale;
Key secondary outcomes	Child mental health; Child self-esteem; Quality of life; Parenting; Mental health knowledge

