### Intervention

LTC is a brief family focused intervention design to be delivered with minimal training [2]. The LTC intervention has been previously translated into Chinese and pilot tested by our study group (unpublished data). Therapists with prior experience working with patients with severe mental illnesses will be recruited to receive LTC training provided by our study team. Remote and on-site supervision will be conducted routinely to ensure treatment quality. The intervention will be delivered to the families in three sessions across one month, of which the first is a preparatory session, with at least one week between session 2 and session 3. Each session will last around 60 min. Therapeutic goals of each session are summarized in Table 2.

**Table 2 Tab2:** Summary of therapeutic goals in each session of ‘Let’s Talk About Children’

Session	Goals
Session 1 (Preparation)	Introduce the intervention. Explore potential concerns about the intervention. Set up future meetings
Session 2	Explore strengths and weaknesses of the child(ren) and concerns about parenting. Each child will be discussed separately. Length of this session may be extended if needed
Session 3	Review the previous session. Discuss impacts of mental illness on parenting. Explore ways parents can help build on strengths and support weaknesses of the child(ren)

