### Statistical analysis

Baseline categorical variables will be summarized as proportion of subjects with the count divided by the total number of evaluated subjects. Baseline continuous variables will be summarized as mean with standard deviation in case of normal distribution and as median with interquartile range in case of non-normal distribution. Efficacy will be assessed in the intention-to-treat population. Missing data will be imputed using the last observation carried forward method. Outcome variables will be differences between pre- and post-test scores at 50 days and 200 days.

Primary outcomes will be compared using t-tests if results conform to a normal distribution and nonparametric tests if they do not. Multivariate generalized linear regression models will be performed with outcome variables as the dependent variable, group allocation as the independent variable, and baseline variables as covariates to account for potential confounding. Data will be analysed as a whole and also separately in the two diagnosis groups. Further subgroups will be explored using interaction tests in the multivariate regression models. Potential subgroup identifiers include but are not limited to child mental health at baseline, parental disease severity, family socioeconomic status and child age. All inferences will be made at a significance level of α = 0.05.

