## Discussion

To our knowledge, this study is the first to assess LTC in families with parental schizophrenia and is the second in families with parental bipolar disorder worldwide. LTC is a brief and simple intervention that has potential to improve mental health and prevent mental disorders in high-risk children. However, LTC has only been tested in limited settings. Previous evidence regarding LTC focuses on families with parental depression [10, 24, 28]. Families with severe parental mental disorders face significantly greater parenting challenges compared to families with parental depression. Parents with severe mental disorders may exhibit violent behaviours, be absent due to hospitalization, or have poorer overall functioning. Severe mental disorders are also more stigmatized than depression [17, 22]. Therefore, families with severe parental mental disorders are in greater need of parenting support. Anecdotal reports of clinicians’ implementation of LTC in families with severe parental mental disorders have been positive [1], however there is a lack of quantitative evidence regarding its efficacy in this population. Therefore, our study will provide valuable information for future clinical practice in families with severe mental disorders worldwide.

Previous research has found that both mothers and fathers with mental illness in China have parenting concerns related to their mental illness [6, 7], however there are currently no evidence-based family focused therapies to address this issue in China. If positive, results from this study will provide much needed treatment option in Chinese speaking families with parental mental illness.

The primary limitation of this study is the inability to blind participants, therapists and research workers to randomization status, which may lead to overestimation of intervention effects because of observer bias. Another limitation is that the therapists participating in this study have no previous experience delivering LTC as this intervention was introduced to China only recently by our study team, which may result in poorer efficacy compared to experienced therapists. Our team will conduct detailed training and supervision throughout the study to ensure fidelity and congruency across different sites.

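### As written, the discontinuation criteria most naturally end outcome assessment at events related to the outcomes, and last observation carried forward then supplies pre-event scores, which undermines the intention-to-treat analysis

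*Protocol article*

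**What the plan says.** The discontinuation criteria stand in Table 1 of the protocol article, in the row on inclusion and exclusion criteria. The first applies when the "patient is hospitalized or visits the emergency room due to their mental illness, or exhibits self-harm, suicidal or aggressive behaviour", or when the patient receives a diagnosis of another severe medical condition. The second reads "During the intervention or follow-up period, the spouse or child(ren) is diagnosed with a severe mental disorder", with a list limited to psychotic and bipolar-type disorders, and again adds severe medical conditions. Both criteria cover the intervention period and the follow-up period.

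On treatment, the Intervention section says "The intervention will be delivered to the families in three sessions across one month". The Control section gives wait-list families usual care and offers LTC only once the study is complete. The follow-up schedule has assessments at baseline, day 50 and day 200.

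On objectives, the primary one is to "assess the efficacy of LTC in improving mental health of children of parents with schizophrenia or bipolar disorder in China" and the first secondary one is to "Assess the efficacy of LTC in improving the mental health of parents experiencing schizophrenia or bipolar disorder". The Discussion adds that "LTC is a brief and simple intervention that has potential to improve mental health and prevent mental disorders in high-risk children".

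On analysis, the Statistical analysis section says "Efficacy will be assessed in the intention-to-treat population". Missing data are filled by last observation carried forward (LOCF), and the outcome variables are changes from baseline at days 50 and 200.

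**The concern.** The article does not define what discontinuation ends. While LTC sessions are under way it could mean stopping the sessions. After about the first month in the LTC arm, and at any time in the control arm, there is no study treatment to stop. For those families the natural meaning is that study assessments stop.

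If so, whether a family is measured depends on events that occur after randomisation and are related to what the trial measures. A parent's hospitalisation or self-harm lies at the poor end of the parental mental health objective and plausibly affects the child. A severe mental disorder in the child lies at the poor end of the primary domain. LOCF then enters a score from before the event, so the analysis cannot see how the family fared afterwards.

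The proportions removed could differ between arms. LTC might prevent such events, in which case part of its benefit is hidden. It might also bring them to light: the trial is unmasked, researchers often share offices with therapists, LTC families have three extra clinical contacts, and aggressive behaviour is a matter of judgement. In that case the LTC arm would lose more poor outcomes and look better than it should.

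**Working it through.** **1. The plan's own figure.** The Sample size section gives a target difference of 3 SDQ points, SD 5, two-sided α = 0.05 and (reading its β of 0.9 as power) 90% power. Per arm, n = 2 × (1.960 + 1.282)² × 5² / 3² ≈ 58.4, so 59 per arm and 118 in total. The t-test version gives 60 per arm, 120 in total, as stated. With 40% dropout, 120 / 0.6 = 200 per diagnosis, also as stated. The point does not rest on this figure; it supplies the 3-point yardstick.

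**2. What LOCF does to a discontinued family.**

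| Time of event | Day-50 change used | Day-200 change used |
|---|---|---|
| Before the day-50 visit | 0 (baseline carried) | 0 (baseline carried) |
| Between the day-50 and day-200 visits | observed | day-50 change carried |

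In each case the carried score predates the event. Events after the day-50 visit, roughly 150 of the 200 days, affect only the day-200 comparison.

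**3. Formula.** Let p_T and p_C be the proportions with a triggering event before day 50 in the LTC and control arms, m_T and m_C the mean change in the other families, and W the mean worsening after an event, taken as equal in both arms. A higher SDQ score is worse, so benefit is control change minus LTC change.

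- True benefit = [(1 − p_C)m_C + p_C W] − [(1 − p_T)m_T + p_T W]
- LOCF benefit = (1 − p_C)m_C − (1 − p_T)m_T
- LOCF minus true = W × (p_T − p_C)

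The same form holds at day 200 for later events, with W measured from the day-50 score. If worsening differs by arm, the bias is p_T W_T − p_C W_C.

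**4. Numbers.** The documents give neither event rates nor W, so both are assumptions.

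- Difference 5 points, W = 5: 0.05 × 5 = 0.25 SDQ points, and 0.25 / 3 = 8% of the target.
- Difference 10 points, W = 6: 0.10 × 6 = 0.6 SDQ points, and 0.6 / 3 = 20% of the target.

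A second set of assumptions takes m_T = −3, m_C = 0 and W from 3 to 5:

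| p_T / p_C | True benefit | LOCF benefit | LOCF minus true |
|---|---|---|---|
| 10% / 10% | 2.7 | 2.7 | 0 |
| 10% / 20% | 3.0 to 3.2 | 2.7 | −0.3 to −0.5 |
| 20% / 40% | 3.0 to 3.4 | 2.4 | −0.6 to −1.0 |
| 20% / 10% | 2.1 to 1.9 | 2.4 | +0.3 to +0.5 |
| 40% / 20% | 1.2 to 0.8 | 1.8 | +0.6 to +1.0 |

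**5. Against the precision of the trial.** With 100 families per arm in one diagnosis and the SD of change assumed to be 5, the standard error is 5 × √(2/100) ≈ 0.71. A bias of 0.25 to 0.6 is then about 0.35 to 0.85 standard errors.

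**6. Which trigger matters most.** The Introduction gives 12.3% to 18.8% of high-risk children developing schizophrenia in adulthood. Spread evenly over an assumed 20 years, that is 0.123/20 × 200/365 ≈ 0.3% to 0.188/20 × 200/365 ≈ 0.5% per 200 days, for schizophrenia alone. Severe child diagnoses are therefore likely to be few, and parental events probably drive most of any effect.

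**The case against.** The strongest reply is that the criteria sit in a condensed registry-style table, that discontinuation is never defined, and that the study flowchart and the assessment schedule are not visible in the text at hand. The full protocol may keep assessing these families. That limits the certainty: one cannot say that post-event outcomes are never measured. It does not remove the point, because the rule is stated, it reaches into a period with no study treatment to stop, and nothing shown says that assessments go on.

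Several stronger readings are tempting, and the documents do not support them:

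- **That the rule contradicts intention-to-treat.** The Statistical analysis section does not drop these families; it keeps them with imputed values.
- **That any psychiatric diagnosis in the child triggers removal.** The mental-disorder part covers only severe, psychotic or bipolar-type conditions, not the emotional, conduct, hyperactivity and peer problems that the SDQ measures.
- **That the clinical global impression scale cannot register relapse.** A relapse that meets none of the listed triggers can still be scored.
- **That harms are lost.** Adverse events are recorded throughout, and site staff record dropouts in the data collection software.
- **That the rule accounts for part of the 40% dropout.** The Sample size section gives no breakdown.

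The criticism of the size also stands. The 5 to 10 points are a difference between arms, not an event rate. A worsening of 5 to 6 points is at least one full stated SD, which is a lot to attach to every trigger, including an emergency visit by the parent or a medical diagnosis. Finally, the numerical harm works through LOCF, which is open to question in its own right.

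**Conclusion.** The point holds in limited form. As written, the criteria most naturally end outcome assessment at post-randomisation events related to the primary and secondary outcomes. The analysis then uses pre-event scores for those families. This is informative missingness created by a stated rule, and it weakens what the intention-to-treat analysis can claim.

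The direction is unknown. If event proportions and worsening are the same in both arms, the between-arm bias is zero. The range of 0.25 to 0.6 SDQ points, 8% to 20% of the target, is an illustration that rests wholly on assumed inputs; the wider assumptions above give 0.3 to 1.0. The view that parental events dominate is likewise an assumption. What makes the point worth acting on is that scores never collected cannot be recovered by analysis, and Table 1 gives recruitment as ongoing.

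**What to change.** Reconcile the discontinuation criteria in Table 1 with the Statistical analysis section:

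- State that meeting a discontinuation criterion does not end data collection. Families in both arms keep the day-50 and day-200 assessments unless consent is withdrawn.
- State that scores observed after such an event, not LOCF values, enter the intention-to-treat analysis.
- Tabulate the triggering events by arm, with their timing relative to the day-50 visit.

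Whether sessions or other care continue after an event is for the clinical rules and is not addressed here. How to handle scores that are still missing, for instance after withdrawal of consent, is a separate question about LOCF.

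The cost is a change of wording, a setting in the data collection software so that these families still receive their questionnaires, and a small extra follow-up effort. The sample size does not change.
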